### 3.4 Outcomes

#### Primary outcome

- **CAL**

The primary outcome is CAL at 6-8 weeks.

CAL will be evaluated by experienced pediatric cardiologists (at least 2 years experience of pediatric 2D echocardiography) using 2D echocardiography. The luminal diameter of left main coronary artery (LMCA) is measured at a point between the ostium and the first bifurcation of the artery (as Figure below). The luminal diameter of left anterior descending artery (LAD) is measured distal to and away from the bifurcation of the branch from the LCA. The luminal diameter of right coronary artery (RCA) is measured in the relatively straight section of the artery just after rightward turn from the initial anterior course of the artery. Definition of CAL is coronary artery luminal diameter greater than  $+3SD$  in one of the three proximal segments or greater than  $+2.5SD$  in two of the three proximal segments. The calculation of Z score is based on the website of Taiwan Society of Pediatric Cardiology ([http://www.tspc.org.tw/service/z\\_score.asp](http://www.tspc.org.tw/service/z_score.asp)).

[figure not shown]

**Figure:** coronary artery luminal diameter measurement in 2D echocardiogram

#### Secondary outcomes

- **IVIG resistance rate:**

IVIG resistance is defined as persistent or recrudescent fever at least 48 hours but not longer than 7 days after completion of the first IVIG treatment.

- **Duration of fever after IVIG treatment**

We will record the body temperature every 6 hour during the hospitalization period.

- **Duration of hospitalization**

We will record the hospitalization duration from admission (or arriving emergency room) to discharge date.

- **Laboratory data**

Laboratory data of CBC/DC, GOT/GPT, and CRP will be checked at baseline, day 5, and 6-8 week.

- **Z score of coronary arteries**

We will estimate Z score of the proximal segments of LMCA, LAD, and RCA at baseline, Day 5, 6-8 weeks, and 6 month with 2D echocardiography. The calculation of Z score is based on the website of Taiwan Society of Pediatric Cardiology ([http://www.tspc.org.tw/service/z\\_score.asp](http://www.tspc.org.tw/service/z_score.asp)).

- **CAL rate at 6 months**

- **Adverse event (AE) and serious adverse event (SAE)**

We will record AE and SAE. Severity of AE will be based on Common Terminology Criteria for Adverse Events (CTCAE) version 4.03.

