**Screen Visit**  
**(Visit 1, Day -3 to 0)**

**Visit Date:** 20□□/□□/□□ (yyyy/mm/dd)

**Admission (or emergency room) date:** 20□□/□□/□□ (yyyy/mm/dd)

**Fever start date:** 20□□/□□/□□/□□ (yyyy/mm/dd/hh)

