**Randomization Visit**  
**(Visit 2, Day 0 to 1)**

**Randomization number assignment date:** 20□□/□□/□□ (yyyy/mm/dd)

**Randomization number:** □□□

☐ **Test group:**

Patient will receive IVIG (2g/kg) in 10-12 hours alone, **without** high-dose aspirin. After fever subsides, low-dose aspirin (3-5mg/kg/day) will be prescribed until 6-8 weeks.

☐ **Standard group:**

Patient will receive IVIG (2g/kg) in 10-12 hours plus high-dose aspirin (80-100mg/kg/day, divided into four doses) till fever subside. After fever subsides, low-dose aspirin (3-5mg/kg/day) will be prescribed until 6-8 weeks.

|                                                                                                                                                   |                                 |             |
|---------------------------------------------------------------------------------------------------------------------------------------------------|---------------------------------|-------------|
| I have reviewed all data recorded on all pages of this visit and certify that they are accurate, complete and consistent to the subject's record. | Investigator's Signature | Date |
|                                                                                                                                                   |                                 |             |

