**Treatment Visit**  
**(Visit 3, Day 1)**

**IVIG treatment:**

start: 20□□/□□/□□/□□, end: 20□□/□□/□□/□□ (yyyy/mm/dd/hh)

**High-dose aspirin treatment** ☐None

start: 20□□/□□/□□/□□, end: 20□□/□□/□□/□□ (yyyy/mm/dd/hh)

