**Body temperature (q4h)**

| Day 1 | °C | Day 2 | °C | Day 3 | °C | Day 4 | °C | Day 5 | °C |
|-------|----|-------|----|-------|----|-------|----|-------|----|
| :     |    | :     |    | :     |    | :     |    | :     |    |
| :     |    | :     |    | :     |    | :     |    | :     |    |
| :     |    | :     |    | :     |    | :     |    | :     |    |
| :     |    | :     |    | :     |    | :     |    | :     |    |
| :     |    | :     |    | :     |    | :     |    | :     |    |
| :     |    | :     |    | :     |    | :     |    | :     |    |

**Fever subside at:** 20□□/□□/□□/□□ (yyyy/mm/dd/hh)

**Antipyretic Drugs:** ☐Ibuprofen ☐Acetaminophen ☐Diclofenac

☐Others: \_\_\_\_\_

**IVIG resistance:** ☐YES ☐No

**Treatment for IVIG resistance:** ☐Second dose of IVIG

☐Others: \_\_\_\_\_

|                                                                                                                                                   |                                 |             |
|---------------------------------------------------------------------------------------------------------------------------------------------------|---------------------------------|-------------|
| I have reviewed all data recorded on all pages of this visit and certify that they are accurate, complete and consistent to the subject's record. | Investigator's Signature | Date |
|                                                                                                                                                   |                                 |             |

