**Day 5 follow up Visit**  
**(Visit 4, Day 3 to 7)**

**Day 5 follow up laboratory data date:** 20□□/□□/□□ (yyyy/mm/dd)

| Item | Value | Unit       | Item       | Value | Unit    | Item       | Value | Unit |
|------|-------|------------|------------|-------|---------|------------|-------|------|
| WBC  |       | 1000/ul    | MCHC       |       | gHb/dl  | Monocyte   |       | %    |
| RBC  |       | Million/ul | RDW-SD     |       | %       | Eosinophil |       | %    |
| HGB  |       | g/dl       | RDW-CV     |       | %       | Basophil   |       | %    |
| HCT  |       | %          | PLT        |       | 1000/ul | AST/GOT    |       | U/L  |
| MCV  |       | fL         | Segment    |       | %       | ALT/GPT    |       | U/L  |
| MCH  |       | pg/cell    | Lymphocyte |       | %       | CRP        |       | mg/L |

**Day 5 follow up 2D echocardiography date:** 20□□/□□/□□ (yyyy/mm/dd)

Performer: \_\_\_\_\_

Body weight: □□.□ Kg

Body height: □□□.□ cm

LMCA: \_\_\_\_\_mm, Z score: \_\_\_\_\_

LAD: \_\_\_\_\_mm, Z score: \_\_\_\_\_

RCA: \_\_\_\_\_mm, Z score: \_\_\_\_\_

Coronary artery lesion: ☐Yes ☐No

Lesion type: \_\_\_\_\_

**Discharge date:** 20□□/□□/□□ (yyyy/mm/dd)

[figure not shown]

|                                                                                                                                                   |                                 |             |
|---------------------------------------------------------------------------------------------------------------------------------------------------|---------------------------------|-------------|
| I have reviewed all data recorded on all pages of this visit and certify that they are accurate, complete and consistent to the subject's record. | Investigator's Signature | Date |
|                                                                                                                                                   |                                 |             |

**Week 6-8 follow up Visit  
(Visit 5, Day 39 to 59)**

**Week 6-8 follow up laboratory data date:** 20□□/□□/□□ (yyyy/mm/dd)

| Item | Value | Unit       | Item       | Value | Unit    | Item       | Value | Unit |
|------|-------|------------|------------|-------|---------|------------|-------|------|
| WBC  |       | 1000/ul    | MCHC       |       | gHb/dl  | Monocyte   |       | %    |
| RBC  |       | Million/ul | RDW-SD     |       | %       | Eosinophil |       | %    |

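### Duration of hospitalization starts before randomisation and ends at a single discharge date, so it carries avoidable noise and can record a child who is discharged and then readmitted as a short stay

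*Combined protocol and SAP*

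**What the plan says.** Duration of hospitalization is a named secondary objective (Synopsis; protocol 2.2). Section 3.4 defines it in one sentence: "We will record the hospitalization duration from admission (or arriving emergency room) to discharge date". Section 3.11 assigns it to the intention-to-treat set.

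The CRF supplies the two ends of the interval:

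- **Start.** The Screen Visit page (Day -3 to 0) asks for "Admission (or emergency room) date". Randomisation follows on a later page ("Visit 2, Day 0 to 1"), and the start and end of "IVIG treatment" are recorded to the hour on the Day 1 page.
- **End.** A single "Discharge date" is entered on the Day 5 follow-up page ("Visit 4, Day 3 to 7"). The CRF pages available have no readmission or second-discharge field, and the protocol has no rule for counting a second stay.

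In the same section, IVIG resistance is "persistent or recrudescent fever at least 48 hours but not longer than 7 days after completion of the first IVIG treatment". The Day 1 page records resistance as yes or no, together with "Treatment for IVIG resistance", but no dates of a further admission.

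**The concern.** Two features of the definition do not serve a comparison of treatments.

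First, the clock runs before treatment is assigned. A child admitted early in the illness must wait until the fever-duration criteria in 3.2 are met, and those days cannot respond to treatment. They enlarge the spread of the outcome.

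Second, the clock stops once. Resistance can appear up to 7 days after IVIG, so it can follow a first discharge. A child discharged and then readmitted for a second treatment may be recorded with a stay that ends at the first discharge, possibly shorter than that of a child who responded and went home once. If such readmissions were more common in one arm, part of that arm's extra hospital time would go unrecorded. Without a field, those days cannot be recovered at analysis from the CRF as shown.

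**Working it through.** **The plan's own figures.** The documents give no power or sample size for hospital stay. The group size used below is the plan's 139 per arm, which reproduces at one-sided 0.05: (1.645 + 0.842)² × (0.846 × 0.154 + 0.83 × 0.17) / (0.016 + 0.10)² = 124.7, so 125; and 125 / 0.9 = 138.9, so 139.

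**Inputs from the documents** (protocol 2.1, retrospective study of 851 children):

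- Resistance 31/305 = 10.2% with high-dose aspirin and 38/546 = 7.0% without.
- Total hospital days 6.3 ± 0.2 against 6.7 ± 0.2, p = 0.13.

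The ± must be a standard error. Read that way, z = 0.4 / √(0.2² + 0.2²) = 1.41 and p = 0.16, which fits the stated 0.13 after rounding. Read as an SD, p would be practically zero. The implied SDs are 0.2 × √305 = 3.5 and 0.2 × √546 = 4.7 days, pooled 4.3.

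**Inputs that the documents do not give (assumptions):** the spread of days before randomisation, the share of resistance that appears after discharge, and the length of a readmission.

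**Step 1: days before randomisation.** Suppose they are uniform over 0 to 3 days and independent of the later stay. Their variance is 9/12 = 0.75 if time is continuous, or 1.25 if counted in whole days.

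- The SD without them is √(SD² − variance). Over SDs of 3.5 to 4.7 days, this is 2 to 5% lower.
- At the pooled SD, the difference detectable with 80% power, two-sided 0.05, is (1.960 + 0.842) × 4.29 × √(2/139) = 1.44 days. Without those days it is 1.39 to 1.41.
- Day -3 limits the screening visit, not the admission date, so the spread could be wider. With an SD of 2 days before randomisation, the total SD would fall by 10 to 18%.

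**Step 2: how one child is scored.** Take an invented child admitted on Day 0, discharged on Day 4, readmitted on Day 6 and discharged on Day 10. Actual inpatient time is 4 + 4 = 8 days. Entering the first discharge gives 4 days, less than a responder who stays from Day 0 to Day 5. Entering the last discharge gives 10 days, two of them at home. No instruction says which date to enter. A child who stays in hospital with persistent fever has one admission and one discharge and is recorded correctly.

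**Step 3: effect on the means.** Days omitted per child = resistance rate × share after discharge × days per readmission. Take a share of 10 to 50% and 4 days.

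- Test arm: 0.070 × 0.10 × 4 = 0.03 to 0.070 × 0.50 × 4 = 0.14 day.
- Standard arm: 0.102 × 0.10 × 4 = 0.04 to 0.102 × 0.50 × 4 = 0.20 day.
- Children affected: from 139 × 0.070 × 0.10 = 1 to 139 × 0.102 × 0.50 = 7 per arm.
- Net distortion between arms: 4 × (0.102 − 0.070) × (0.10 to 0.50) = 0.01 to 0.06 day.

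**Step 4: wider assumptions.** If every resistant child were readmitted for 5 days, the omissions would be 0.51 and 0.35 day, a net 0.16 day. If one arm had 10 points more failures, the hidden excess would be 0.10 × 4 × (0.10 to 0.50) = 0.04 to 0.20 day, or 0.03 to 0.50 day over shares of 10 to 100% and stays of 3 to 5 days. The standard error of the difference is about 4.29 × √(2/139) = 0.51 day.

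**The case against.** The strongest reply is that little is at stake. Much of it stands.

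- **A reader might infer that days before randomisation bias the comparison or shrink the difference.** They do not. They precede allocation, add equally to both arms in expectation and leave the difference in days unchanged. Only precision suffers, and the CRF already holds the dates needed to remove them.
- **A reader might infer that treatment failures in general are scored in the wrong direction.** Only those discharged and then readmitted can be. The documents do not say how often that happens. A retrospective mean stay of 6.3 to 6.7 days and a temperature chart running to Day 5 do not suggest that very early discharge is usual. Nothing confines the discharge date to the window printed on its page.
- **A reader might set the 0.03 to 0.20 day against the retrospective difference of 0.4 day.** That compares a shift within an arm with a difference between arms. The like-for-like figure is 0.01 to 0.06 day.
- **A reader might expect more relapse after discharge in the standard arm because high-dose aspirin is stepped down there.** The documents offer no evidence for this.
- **Failure is not hidden.** Resistance is its own secondary outcome, and its treatment and the concomitant medications are recorded.

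What does not stand is the idea that other records fill the gap. The medication log may date a second treatment but not a second discharge. Section 3.12 stops adverse event recording at discharge and counts a hospitalisation as serious only if it is believed related to treatment. The timeline in 3.5 marks adverse events at 6-8 weeks, and the two sections must be reconciled, but neither records length of stay. The SAE form named in 3.12 was not among the pages reviewed, so the absence of a readmission field is established only for the CRF pages available.

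**Conclusion.** The point holds as a cheap improvement to one secondary outcome. The definition starts before randomisation and has no rule for a second stay, so it can record a discharged and readmitted child as a short stay.

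At the retrospective resistance rates the likely damage is small: a few per cent of SD, and a net shift between arms that is at most about an eighth of the standard error (0.06 / 0.51). It becomes material only if failure rates differ much more between arms than in the retrospective data, or if readmission is far more common than assumed. The spread of days before randomisation, the share of resistance after discharge and the length of a readmission are all assumptions.

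**What to change.** In 3.4, define the outcome as total inpatient days from the randomisation date to a fixed day, including readmissions within that period. The day should cover the 7-day resistance window and fall before Day 39, the earliest Visit 5 date; Day 28 is an example. Starting at randomisation needs no new data, because the date is on the Visit 2 page, and it keeps every randomised child in the intention-to-treat set. A fixed end gives all children the same horizon, which counting to a visit between Day 39 and Day 59 would not.

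Add one line to the Visit 5 page for the admission and discharge dates of any readmission. Report admission to first discharge as a descriptive figure.

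Costs:

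- One CRF line and one sentence in 3.4.
- Missing readmission data for children lost before Visit 5. At the planned maximum dropout of 10% this could be about 14 of 139 per arm, more than the 1 to 7 children whose stay is corrected. Their first stay is still known, so run a sensitivity analysis using the first discharge date.
- Readmissions unrelated to Kawasaki disease are included.
- The figure is less directly comparable with total hospital days in the retrospective study, which the descriptive figure partly offsets.

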(n=305) and Group 2, IVIG without high-dose aspirin (n=546). There are no significant differences between groups 1 and 2 in terms of gender ( $p=0.51$ ), IVIG resistant rate (31/305 vs. 38/546,  $p=0.07$ ), CAL formation rate (52/305 vs. 84/546,  $p=0.67$ ), and total hospital days ( $6.3\pm0.2$  vs.  $6.7\pm0.2$ ,  $p=0.13$ ). These retrospective observational data suggest that aspirin offers little additional benefit to IVIG therapy.

There is still no good quality of randomized control trial (RCT) to evaluate whether children with KD should continue to receive high-dose aspirin as part of their treatment regimen. Cochrane Vascular Group reviewed RCTs of aspirin to treat KD in children.[17] The review authors identified only one RCT (multicenter, 3-arms design), from Japan reported in 1991. Furusho et al compared IVIG and aspirin treatment with aspirin alone, and with IVIG alone.[18] The dose of aspirin was 30 to 50 mg/kg/day in three divided doses until the fever had subsided, then 10 to 30mg/kg/day once a day until “the acute reaction had also disappeared.” Children were enrolled if they presented within seven days of the onset of symptoms. Children with recurrent KD and with CAL at presentation were excluded. Children in the two groups (IVIG with aspirin and IVIG alone) did not differ significantly in respect to age at presentation, sex, or time from onset of symptoms to trial entry. The incidence of new CAL prior to 30 days from onset of symptoms were 18.4% (9 of 49) in children receiving IVIG and aspirin and 18.9% (10 of 53) in children receiving IVIG alone. The relative risk (RR) was 0.97 and 95% confidence intervals (CI) was 0.43 to 2.19. The prevalence of CAL at 30 days after the onset of symptoms were 10.2% (5 of 49) in children receiving IVIG and aspirin and 7.8% (4 of 51) in children receiving IVIG alone. The RR was 1.30 and 95% CI was 0.37 to 4.56.

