## **2.2 Objectives**

### **Primary objective**

- To assess whether IVIG alone as the primary therapy in acute stage of KD is non-inferior to IVIG plus high-dose aspirin therapy in preventing the development of CAL at 6-8weeks.

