### 3.5 Participant timeline

| Study period       | Enrolment | Randomization | Intervention | Day 5   | 6-8 weeks | 6 months   |
|--------------------|-----------|---------------|--------------|---------|-----------|------------|
| Time point         | Day -3~0  |               | Day 1        | Day 5±2 | Day 49±10 | Day 180±30 |
| Eligibility screen | •         |               |              |         |           |            |
| Informed consent   | •         |               |              |         |           |            |
| Demographics       | •         |               |              |         |           |            |
| Randomization      |           | •             |              |         |           |            |
| Intervention       |           |               | •            |         |           |            |
| echocardiography   |           |               |              | •       | •         | •          |
| Body temperature   | •         |               |              | •       | •         |            |
| CBC/DC             | •         |               |              | •       | •         |            |
| GOT/GPT            | •         |               |              | •       | •         |            |
| CRP                | •         |               |              | •       | •         |            |
| AE、SAE             |           |               | •            | •       | •         |            |
|                    |           |               |              |         |           |            |

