**Demographic Data**

**Gender:** ☐ Male ☐ Female, **Birthday:** □□□□/□□/□□ (yyyy/mm/dd)

**Body weight:** □□.□ Kg, **Body height:** □□□.□ cm, **Body temperature:** □□.□ °C

**Baseline laboratory data date:** 20□□/□□/□□ (yyyy/mm/dd)

| Item | Value | Unit       | Item       | Value | Unit    | Item       | Value | Unit |
|------|-------|------------|------------|-------|---------|------------|-------|------|
| WBC  |       | 1000/ul    | MCHC       |       | gHb/dl  | Monocyte   |       | %    |
| RBC  |       | Million/ul | RDW-SD     |       | %       | Eosinophil |       | %    |
| HGB  |       | g/dl       | RDW-CV     |       | %       | Basophil   |       | %    |
| HCT  |       | %          | PLT        |       | 1000/ul | AST/GOT    |       | U/L  |
| MCV  |       | fL         | Segment    |       | %       | ALT/GPT    |       | U/L  |
| MCH  |       | pg/cell    | Lymphocyte |       | %       | CRP        |       | mg/L |

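### The baseline echocardiogram promised in Protocol 3.4 is missing from the visit schedule and the CRF, so coronary status at entry may go unrecorded

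*Combined protocol and SAP*

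**What the plan says.** Protocol 3.4, under secondary outcomes, commits to four echocardiographic time points: "We will estimate Z score of the proximal segments of LMCA, LAD, and RCA at baseline, Day 5, 6-8 weeks, and 6 month".

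The schedule in Protocol 3.5 has a row for "echocardiography" with three marks: Day 5, 6-8 weeks and 6 months. Its enrolment, randomisation and intervention cells are empty, although body temperature, CBC/DC, GOT/GPT and CRP are all marked at enrolment.

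The CRF in Appendix B follows the schedule:

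- Visit 1 (Screen, Day -3 to 0) has demographics, weight, height, temperature and a laboratory block headed "Baseline laboratory data date", but no echo block.
- Visit 2 (Randomization, Day 0 to 1) has "Randomization number assignment date", the number and the arm.
- Visit 3 (Treatment, Day 1) has IVIG times, "High-dose aspirin treatment", low-dose aspirin, temperatures, antipyretics and IVIG resistance.
- Visit 4 (Day 3 to 7) has the first echo field, "Day 5 follow up 2D echocardiography date", followed by diameters, Z scores and a CAL yes/no box.

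None of the 12 exclusion criteria in Protocol 3.2 concerns CAL at entry. The primary objective (2.2) is non-inferiority "in preventing the development of CAL at 6-8weeks", and section 2.3 calls the endpoint CAL formation. Sections 3.4 and the Synopsis define it simply as CAL at 6-8 weeks, with no reference to status at entry.

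**The concern.** The outcomes section requires a measurement that the two documents sites work from do not ask for. If sites follow the schedule and CRF, there is no recorded coronary measurement before treatment. The Day 5 echo cannot stand in for it, because IVIG and, in the standard group, high-dose aspirin start on Day 1.

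Three things would then be lost, and no later analysis can recover them:

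- **New versus existing lesions.** Children can enter with up to ten days of fever and with a lesion already present. The wording about development and formation implies new lesions, but the data could not identify them. The earlier randomised trial described in section 2.1 dealt with this at entry: "Children with recurrent KD and with CAL at presentation were excluded".
- **Comparability.** Protocol 3.11 uses baseline characteristics to judge whether the arms are comparable. The baseline value of the endpoint measurement itself would not be among them.
- **Adjustment.** Follow-up Z scores could not be analysed against their baseline, and the primary risk difference could not be adjusted for it.

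**Working it through.** **1. The plan's own figure.** Protocol 3.6 gives CAL-free rates of 0.846 (test) and 0.83 (standard), a margin of 0.10, α = 0.05 and 80% power. With one-sided α = 0.05:

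n = (1.645 + 0.842)² × (0.83×0.17 + 0.846×0.154) / (0.016 + 0.10)² = 6.18 × 0.2714 / 0.01346 ≈ 124.7, so 125 per group.

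125/0.9 = 138.9, so 139 per group and 278 in total. The stated figures reproduce. None of these inputs depends on the baseline echo.

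**2. The time points side by side.**

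| Time point | 3.4 Outcomes | 3.5 Schedule | CRF |
|---|---|---|---|
| Baseline | yes | no | no (Visits 1-3) |
| Day 5 | yes | yes | yes (Visit 4) |
| 6-8 weeks | yes | yes | yes (Visit 5) |
| 6 months | yes | yes | yes (Visit 6) |

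The only disagreement is at baseline, and the schedule and CRF agree with each other against 3.4.

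**3. Chance imbalance in CAL at entry.** The documents give no baseline prevalence b, so a range is assumed. With 125 per arm, the SD of the between-arm difference is √(2b(1−b)/125). The 95% range is ±1.96 SD, and the chance of an imbalance above 5 points in either direction is 2[1 − Φ(5/SD)], with SD in points.

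| Assumed b | SD (points) | 95% range (points) | Chance of more than 5 points |
|---|---|---|---|
| 5% | 2.8 | ±5.4 | 7% |
| 10% | 3.8 | ±7.4 | 19% |
| 15% | 4.5 | ±8.9 | 27% |
| 20% | 5.1 | ±9.9 | 32% |

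For example, at 10%: √(2×0.10×0.90/125) = √0.00144 = 0.038. These are imbalances at entry. They carry through to 6-8 weeks only so far as the lesions persist.

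**4. Precision from adjustment.** The correlation ρ between baseline and follow-up Z is also an assumption. The model is simplified: one baseline and one follow-up Z per child, bivariate normal, with the threshold set so that 17% have CAL, and a standardised risk difference from a logistic model. In 1,500 simulated trials at 125 per arm, the ratio of adjusted to unadjusted variance was 0.96, 0.90 and 0.72 at ρ = 0.3, 0.5 and 0.7. A second simulation gave reductions of about 4%, 11% and 25%.

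A hand check uses the linear share of variance explained, ρ²φ(c)²/[p(1−p)]. With p = 0.17, c = 0.954 and φ(c) = 0.253, this is ρ² × 0.0640/0.1411 = 0.454ρ², or 4%, 11% and 22%. The last value is lower than the simulations because the true relation is curved.

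**The case against.** **The omission may be clerical.** Section 3.4 is operative protocol text, section 3.10 says echocardiography data go on the CRF, and the schedule is loose elsewhere: temperature has no mark on Day 1, yet the CRF records it from Day 1. Sites may therefore do the baseline echo anyway. That stands, and the loss is conditional on sites following the schedule and CRF. Even if the echo is done, however, the CRF has no place for the result. A few pages are missing from the public file as read, but all six visit pages are there.

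**The primary test needs no baseline value.** CAL at 6-8 weeks can be compared as it is. Randomisation balances lesions at entry in expectation, and the ordinary confidence interval already allows for chance imbalance as sampling error. This stands in full.

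**Stronger readings that the documents do not support.**

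- A reader might infer that lesions present at entry bias the trial towards non-inferiority. If a quarter, half or three quarters of the planned 17% were present at entry and persisted, b would be 4.25%, 8.5% or 12.75%. A 10-point overall difference would then be 10/(1−b) = 10.4, 10.9 or 11.5 points among children free of CAL at entry. On the scale of the margin, the dilution is about 0.4 to 1.5 points. Expressed as a ratio it looks larger, but that reflects a fixed absolute margin set against a low event rate, not the missing echo.
- Persistence is itself doubtful. In the earlier trial described in section 2.1, new CAL before 30 days was 18.4% and 18.9%, but prevalence at 30 days was 10.2% and 7.8%. Many lesions evidently resolved within weeks. Lesions present at entry may do the same, possibly at different rates by arm, so they cannot be treated as fixed events common to both arms.
- A reader might take baseline Z to be the strongest predictor of the endpoint. The documents contain no data on that.

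Baseline adjustment also does not change what the margin tolerates, because it targets the same population difference. Only an analysis of new CAL addresses the wording about development.

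**Conclusion.** The plan contradicts itself: the baseline Z score is a stated secondary measurement in Protocol 3.4, and the schedule and CRF omit it. This should be fixed, because a pre-treatment measurement that is not taken is lost for good. It does not invalidate the primary comparison, which remains unbiased in expectation for CAL present at 6-8 weeks.

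The losses are threefold. New and existing lesions cannot be separated, so the result would not match the stated objective. A chance imbalance in entry lesions would go unseen; it could plausibly reach about 5 to 10 points if baseline prevalence is 5% to 20%. Precision is forgone, ranging from small (about 4% of variance at ρ = 0.3) to useful (25-28% at ρ = 0.7). The prevalence and the correlations are assumptions; the documents supply neither. The contradiction itself rests on no assumption.

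**What to change.** 1. Reconcile section 3.4 with section 3.5 and the CRF. Mark echocardiography in the enrolment column, and copy the Day 5 echo block (date, performer, diameters, Z scores, CAL yes/no) to the Screen Visit page, to be done before study treatment.
2. State in sections 2.2, 2.3 and 3.4 that the primary endpoint is any CAL at 6-8 weeks, so that development and formation are not read as new lesions only. On that definition the sample size is unchanged; it would need revision only if the primary endpoint became new CAL.
3. In section 3.11 and the SAP, pre-specify the risk difference adjusted for baseline maximum Z (standardised from a logistic model, for example), reported beside the unadjusted difference.
4. Add a supportive analysis of new CAL among children without CAL at baseline.
5. Analyse follow-up coronary Z scores by ANCOVA on baseline Z, and list baseline coronary status in the comparability table.

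The cost is one schedule mark, one CRF block and a few sentences of analysis text, put through the amendment process in section 4.2. No procedure is added beyond what section 3.4 already promises.
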